### Outcomes

2.5

Primary outcomes are pain score at different time point. Visual analog scale is used to assess the pain (10: the maximum possible pain and 0: absent pain).^[15]^ The secondary outcomes are the postoperative complications, length of hospital stay and total consumption of opioid.

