## Introduction

1

Total hip replacements (THRs) are quite successful surgery for many end-stage hip diseases in terms of pain relief and functional recovery.^[1,2]^ And the demand for primary THR is projected to grow by 3.48 million procedures in the United States alone by 2030.^[3,4]^ However, THR are associated with severe perioperative pain which prolongs length of hospitalization and increases the morbidity and medical cost.^[5,6]^ Adequate pain management is crucial for improving the satisfaction of patients and clinical outcomes. Numerous strategies have been implemented to reduce postoperative pain following THR including local infiltration analgesia, epidural analgesia, intravenous non-steroidal anti-inflammatory agents and peripheral nerve block.^[7–9]^ Each method has its limitations and opioids are used as an alternative method to reduce pain. However, opioid can cause many side effects, such as gastrointestinal reactions, respiratory depression, retention of urine and constipation.^[10,11]^ Therefore, multimodal analgesia has been extensively used in perioperative period of THR.

Fascia iliaca compartment block (FICB) is a kind of anterior method to lumbar plexus. The hip joint is supplied via the branches of sciatic, obturator, and femoral nerves.^[12]^ They are all the part of lumbar plexus, which means that blocking lumbar plexus provides an elegant method for the postoperative analgesia after THR. FICB has no effect on muscle strength of quadriceps femoris and theoretically, it will not increase the risk of fall during rehabilitation. Several articles have suggested that FICB was related to the reduced consumption of opioid analgesics and the improvement of pain relief in patients with THR.^[13,14]^ However, others reported that there was no positive effects for postoperative pain management.

It is not clear that whether FICB is a kind of effective approach for the postoperative analgesia after THR. Therefore, we conduct this randomized controlled study protocol in order to evaluate the efficacy and safety of FICB for analgesia after THR. Our assumption is that FICB could reduce the consumption of opioid and pain score after operation in the early postoperative period.

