### Subjects

2.1

100 patients undergoing THR will be included in this study. In the random envelope, all participants will be assigned a random number via utilizing the random number table, and the result of allocation is hidden. Patients are randomly divided into 2 groups: FICB group (n = 50) or Non-FICB group (n = 50), FICB with 5mgmL^−1^ of epinephrine and 40 mL of ropivacaine 0.2%. Physicians, statisticians, data collectors and evaluators are all blinded to the allocation.

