### Statistical analysis

2.6

All the needed analyses are implemented through utilizing SPSS for Windows Version 15.0. All the data are represented with proper characteristics as median, mean, percentage as well as standard deviation. Independent samples *t-*test or the Mann-Whitney *U* test is utilized for the comparison between groups. Chi-square detection is utilized to compare the categorical variables among the groups. A *P* < .05 is regarded the significant in statistics.

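### Pain scores at several time points are all primary and share one unadjusted P < .05, with no rule for what counts as a positive result

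*Protocol article*

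**What the plan says.** Section 2.5 (Outcomes), in the same words as the Methods paragraph of the Abstract, states: "Primary outcomes are pain score at different time point". The scale is a 0 to 10 VAS. Complications, hospital stay and total opioid use are secondary.

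Section 2.6 (Statistical analysis) names the comparison for continuous measures: "Independent samples *t-*test or the Mann-Whitney *U* test is utilized for the comparison between groups". It then gives one criterion: "A *P* < .05 is regarded the significant in statistics".

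The Introduction narrows the hypothesis only in general terms: "Our assumption is that FICB could reduce the consumption of opioid and pain score after operation in the early postoperative period". Section 2.1 (Subjects) allocates 50 patients to each arm.

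The visible text has no designated time point, summary measure, hierarchy, repeated-measures model, multiplicity adjustment or success rule. The Results section refers to Figure 1 for the outcomes. That figure is not shown and may list the assessment times.

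**The concern.** The tests in section 2.6 each compare two groups on one value per patient. Applied to scores at several times, they give one P value per time. All of these are primary and all are judged against .05, so the document does not say which P value, or which pattern of P values, answers the trial's question.

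Two things are at stake. If a difference at any one time may be claimed as the primary result, the chance of a false claim is above the nominal 5%. And if the results are mixed, for example a difference early and none later, the plan gives no way to call the trial positive or negative. The article describes the question as controversial and wants the trial to provide evidence on it, so an undetermined primary conclusion weakens what the trial can deliver.

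**Working it through.** **Inputs from the protocol article**
- Arm size: 50 per arm (2.1).
- Per-test threshold: .05, unadjusted (2.6).
- Tests: two-sample t or Mann-Whitney (2.6).

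**Assumptions, because the visible text does not give them**
- Tests are two-sided.
- The number of time points k runs from 2 to 8.
- The correlation ρ between one patient's scores runs from 0 to 0.7.
- Success means P < .05 at any time point. This is one permitted reading, not a stated rule.

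**Step 1: the plan's own figure.** For one test, 1 − 0.95^1 = 5%, so the stated threshold holds if there is a single primary comparison. The total of 100 patients cannot be reproduced, since no effect size, SD or power is given.

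**Step 2: independent scores.** P(at least one false positive) = 1 − 0.95^k. For k = 4: 1 − 0.8145 = 18.55%.

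**Step 3: equally correlated scores.** With c = 1.96, φ the standard normal density and Φ its distribution function:

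P = 1 − ∫ φ(u) [Φ((c − √ρ·u)/√(1−ρ)) − Φ((−c − √ρ·u)/√(1−ρ))]^k du

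| k | ρ = 0.7 | ρ = 0.5 | ρ = 0 |
|---|---|---|---|
| 2 | 8.35% | 9.07% | 9.75% |
| 3 | 10.92% | 12.54% | 14.26% |
| 4 | 13.04% | 15.58% | 18.55% |
| 5 | 14.84% | 18.28% | 22.62% |
| 6 | 16.42% | 20.73% | 26.49% |
| 8 | 19.09% | 25.01% | 33.66% |

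Simulated t-tests with 50 per arm (20,000 trials per setting, k = 3 to 6, ρ = 0.3 to 0.7) agree with the integral to within about 0.5 percentage points. Correlation that decays with time gives somewhat higher rates, for example 16.6% for k = 4 with ρ = 0.5 between neighbouring scores. Even at ρ = 0.9, four time points give 9.4%.

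**Step 4: the opposite rule.** If every time point had to be significant in the same direction, the false-positive rate at ρ = 0.5 would be 0.32% (k = 3), 0.15% (k = 4) or 0.08% (k = 5), and lower still for independent scores. The two readings thus fall on opposite sides of 5%, and the text does not choose between them.

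**Step 5: what a repair does to power.**
- One score, 50 per arm, 80% power, two-sided 5%: (1.960 + 0.842) × √(2/50) = 0.560 SD; allowing for the t distribution, 0.566 SD.
- Bonferroni over five scores (two-sided 1% each): (2.576 + 0.842) × √(2/50) = 0.684 SD; with the t distribution, 0.695 SD at a given time point.
- Equally weighted mean of five scores at ρ = 0.5: variance (1 + 4 × 0.5)/5 = 0.60 of a single score, so the detectable mean effect is 0.566 × √0.60 = 0.438 SD.
- That gain requires the same effect at all five times. With an effect at only 3 of 5 times, 0.438/0.6 = 0.73 SD is needed at each affected time. With 2 of 5 it is 0.438/0.4 = 1.10 SD.

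**The case against.** Several points against the concern have force.

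- **The size cannot be fixed.** A reader might infer that the error rate is about three times nominal. That holds only for particular combinations, such as 3 independent time points, 4 at correlation 0.5 or 5 at correlation 0.7. The document supplies none of these inputs, so only a range can be defended.
- **No any-one-suffices rule is stated.** A reader might infer that one significant time point counts as a positive trial. The text allows this but does not say it, and the stricter rule would bring the error far below 5%. What stands is that the rule is undefined.
- **Separate testing is an inference.** Section 2.6 does not say in words that each time point is tested on its own. It is the natural reading, because neither named test can handle repeated scores jointly.
- **The tests themselves are sound.** A two-sample comparison at one time is valid whatever the correlation across times. Naming a t-test or Mann-Whitney test is ordinary wording for choosing by distribution. It is no evidence that both would be run and the smaller P value kept.
- **This is a condensed article.** The assessment times may be in the figure that is not shown, and the mechanics of a multiplicity procedure may be in an analysis plan. The missing list of times therefore carries no weight here.

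The last objection does not dispose of the point. Which outcome is primary is a matter for the protocol. The article has an outcomes section and an analysis section, and together they fix the primary outcome as an open set judged by one unadjusted threshold. A list of times would supply k but would not by itself single out a primary comparison.

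**Conclusion.** The point holds as a defect in how the primary outcome is fixed: several pain scores are primary, one unadjusted threshold applies, and nothing in the text determines when the primary result is positive. If any significant time point is taken as success, the false-positive rate is roughly 8% to 34% instead of 5% for 2 to 8 time points and correlation from 0.7 down to 0, and 13% to 19% for 4 time points. These figures rest on two-sided tests and on assumed values for k, ρ and the success rule. That the rate exceeds 5% on this reading does not depend on the particular values; how far it exceeds 5% does. A single multiplier, or a claim that the protocol adopts the any-time-point rule, goes beyond what the document supports.

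**What to change.** Before unblinded data are seen:

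1. In 2.5, name one primary outcome. This can be VAS at one stated time point, or one summary such as the time-weighted mean VAS over a stated early window. The clock must be defined identically in both arms and must not count time before the block. Section 2.3 (Anesthesia) places the block after transfer to the ward, so a clock from end of surgery would include unblocked time. The start of patient-controlled analgesia, which 2.3 describes for both groups after the block, is one candidate.
2. In 2.6, test that outcome once at two-sided 5% and report the mean difference with its 95% CI. Make the other time points secondary.

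Alternatively, keep all time points primary and apply a Holm correction. This holds the familywise rate at 5% whatever the correlation; with 4 time points the smallest P value is compared with 0.05/4 = 0.0125.

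The cost is about two sentences, with no added patients or measurements. There are two downsides. An isolated difference at one time can no longer be claimed, unadjusted, as the primary result. And a mean over the window loses power if the effect is confined to a few of the time points, as step 5 of the working shows, so the window should be chosen with the expected duration of effect in mind.

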### Statistical analysis

2.6

All the needed analyses are implemented through utilizing SPSS for Windows Version 15.0. All the data are represented with proper characteristics as median, mean, percentage as well as standard deviation. Independent samples *t-*test or the Mann-Whitney *U* test is utilized for the comparison between groups. Chi-square detection is utilized to compare the categorical variables among the groups. A *P* < .05 is regarded the significant in statistics.

## Results

3

Figure 1 will show the primary and secondary outcomes.

**Figure 1 F1:**
[figure not shown]
Primary and secondary outcomes between FICB group and non-FICB group. FICB = fascia iliaca compartment block.

## Discussion

4

Pain management after the total joint arthroplasty is still challenging, but worthy of attention, because good pain management can improve the outcomes of patient.^[16]^ About 6 to 10 percent of the patients may experience moderate to severe pain lasting at least 3 months after the operation, which is considered as the chronic postoperative pain.^[17]^ Different institutions have different postoperative treatment protocols, which may lead to different techniques used and patterns, and affecting long-term results and success. The lack of a definitive “gold standard” and various postoperative pain treat programs indicate that there is considerable room for improving the standard of care. The techniques of regional anesthesia can decrease postoperative pain scores and the consumption of opioid, so as to improve patient satisfaction and better treatment outcomes.^[18,19]^ It is still controversial whether FICB can effectively decrease the opioid consumption and pain after THR owing to the number of published investigations is small. We conduct this protocol to evaluate the safety and efficacy of FICB in postoperative analgesia after THR.

## Conclusion

5

This trial can provide an evidence for the use of FICB for analgesia after THR.
